### Statistical analysis

#### Sample size calculation

The sample size calculation is performed using GLIMMPSE32 and based on published data on MASA-C scores [49]. A total sample size of 111 participants (37 per group), is needed to demonstrate a different evolution over time in the experimental groups and the control group at a significance level of 0.05 and a power of 0.8 when using repeated measures with Geisser-Greenhouse correction (3 groups × 4 time points). Based on previous research on prophylactic swallowing exercises by Carnaby-Mann and colleagues [19], we expect a baseline MASA-C score of 195, with a decay in the first 6 weeks to 171 in the control group, 177 in the app group and 180 in the therapist group. After 6 weeks we assume no further decline. A standard deviation of 11 is considered for the MASA-C scores at each time point, this is also based on the standard deviations (SDs) reported in Carnaby-Mann et al. [19]. First-order auto-regressive correlation (AR [1]) is assumed for the covariance structure between the repeated measures, with a base correlation of 0.4 and a decay rate of 0.5. The targeted total sample size, taking into account more than 20% dropouts, is 150 (*n* = 50/group).

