#### Data analysis

Patients will be analyzed in the groups to which they are assigned (intention-to-treat). Descriptive statistics will be used to summarize patient characteristics per treatment group. Data will be analyzed using linear mixed-effects models with group, time and group by time interaction as fixed effects. A random intercept will be added to account for correlation between measurements coming from the same individual. When one or more overall effects are significant, post-hoc pairwise testing with Bonferroni-Holm correction for multiple testing will be performed. Missing data is assumed to be missing at random (MAR) and, thus, will be ignored in the analyses. By using mixed-effects models for the analysis, we can incorporate all information on the available time points. If more than 15% of the data is missing, a sensitivity analysis will be conducted by using multiple imputation. Results of the original analysis of the available cases will be interpreted in the context of sensitivity analysis.

Additionally, the impact of adherence, HPV status, dosimetry and mucositis on the different functional endpoints will be studied in exploratory linear mixed-effects models. Fixed main-effects and interactions with group for all these factors will be evaluated.

More details on the primary, secondary and exploratory analyses can be found in the statistical analysis plan.

A *p* value of less than 0.05 will be considered statistically significant. All analyses will be conducted using SPSS Statistics version 25 (IBM, Chicago, IL, USA) and R software (R Foundation, Auckland, New Zealand).

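### The 80% power at 37 per group belongs to the three-group group-by-time test under slowly falling correlations mislabelled AR(1), and should not be read as power for each experimental arm against control

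*Protocol article*

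**What the plan says.** In the protocol article, Sample size calculation: "A total sample size of 111 participants (37 per group") are required for 80% power at the 5% level, "when using repeated measures with Geisser-Greenhouse correction (3 groups × 4 time points"). The aim of that test is described as what "is needed to demonstrate a different evolution over time in the experimental groups and the control group". The assumed mean MASA-C score is 195 at baseline, "with a decay in the first 6 weeks to 171 in the control group, 177 in the app group and 180 in the therapist group", and the means are held flat from then on. The SD is 11 at every time point. The correlation is called first-order autoregressive, "with a base correlation of 0.4 and a decay rate of 0.5". The recruitment target is 150 (50 per group), allowing for more than 20% dropout.

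Under Data analysis, a significant overall effect leads to "post-hoc pairwise testing with Bonferroni-Holm correction". The contrast to be compared pairwise is not fixed there, and no pairwise power is stated anywhere in the article.

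**The concern.** There are two separate problems.

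First, AR(1) has one parameter, but the text gives two. A reader who takes the label at its word and uses 0.4 at lag one, 0.16 at lag two and 0.064 at lag three does not recover 37 per group.

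Second, the trial compares two delivery models with a control, so its practical conclusions come from pairs. The sizing sentence speaks of the experimental groups and the control group, which invites the reading that each arm has 80% power against control. An omnibus test can be significant because of the assumed 9-point therapist-control gap alone. If a non-significant app-control or therapist-app result is then reported against a background of 80% power, it may be taken as evidence of no difference.

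**Working it through.** **Inputs** (Sample size calculation): means 195 then 171/177/180, flat afterwards; SD 11 (variance 121); 37 per group; alpha 0.05. The four time points are not listed in that paragraph. I assume baseline, end of CRT, and 1 and 3 months after, run both equally spaced and at 0/6/10/18 weeks.

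**Correlations.** Reading the decay rate as slowing the fall, ρ(d) = 0.4^(1 + 0.5·(d − dmin)/(dmax − dmin)). With equal spacing this gives 0.4^1 = 0.40, 0.4^1.25 = 0.32 and 0.4^1.5 = 0.25. True AR(1) gives 0.40, 0.16 and 0.064.

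**The plan's own figure.** The post-treatment means average 176, so the group deviations are −5, 1 and 4, with squares summing to 42. With one baseline and three equal post-treatment times, the interaction sum of squares is 37 × 42 × 3/4 = 1165.5. The within-subject error trace is 121 × (4 − S/4), where S is the sum of all 16 correlations.
- Two-parameter structure: S = 4 + 2(3×0.40 + 2×0.318 + 0.253) = 8.18, trace 236.6. Noncentrality before correction is 1165.5/(236.6/3) = 14.8; epsilon is 0.98.
- AR(1): S = 4 + 2(1.2 + 0.32 + 0.064) = 7.17, trace 267.2. Noncentrality is 1165.5/(267.2/3) = 13.1; epsilon is 0.90.

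A noncentral-F approximation for the Geisser-Greenhouse test gives 0.817 at 37 per group with equal spacing (36 would suffice). At 0/6/10/18 weeks it gives 0.812, and 37 is the smallest size reaching 0.80, which matches the article. Simulation gives 0.81 for both spacings. Under AR(1), power is 0.73 to 0.74 and 43 per group are needed. That is 129 evaluable, available from 150 if dropout is at most 1 − 129/150 = 14%.

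**Pairs at 37 per group, two-parameter structure.** Hand check for app-control (6 points), equal spacing:
- Average change: variance 121 × [1 + (3 + 2×1.118)/9 − (2/3)×0.971] = 113.1; SE = √(2×113.1/37) = 2.47; 6/2.47 = 2.43; unadjusted power about 0.67.
- Change to last visit: variance 121 × 2 × (1 − 0.253) = 180.8; SE 3.13; ratio 1.92; about 0.48.
- Post-treatment mean without baseline: variance 121 × 5.236/9 = 70.4; SE 1.95; ratio 3.08; about 0.86.
- Baseline-adjusted post-treatment mean: variance 70.4 − 121 × (0.971/3)² = 57.7; SE 1.77; ratio 3.40; about 0.92.

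Simulation (20,000 replicates) adds the Holm step and, in the last two columns, the requirement of a significant group-by-time test:

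| Pairwise contrast | App-control, unadjusted | App-control, Holm | App-control, Holm and gate | Therapist-control, Holm and gate |
|---|---|---|---|---|
| 2 × 4 interaction | 0.51 | 0.40 | 0.39 | 0.76 |
| Average change | 0.67 | 0.57 | 0.54 | 0.80 |
| Change to last visit | 0.48 | 0.35 | 0.35 | 0.65 |
| Post-treatment mean, no baseline | 0.87 | 0.82 | 0.68 | 0.80 |
| Baseline-adjusted post-treatment mean | 0.92 | 0.90 | 0.75–0.76 | 0.81 |

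Therapist-app (3 points) has about 0.11 to 0.19 on the three change-based rows. Even with baseline adjustment its ratio is only 3/1.77 = 1.70, so unadjusted power stays below 0.40.

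**The case against.** The strongest defence is that nothing has been miscalculated. The sizing sentence goes on to name three groups and four time points, which identifies the omnibus test. The pairwise tests are called post hoc, and both correlation parameters are printed. All of this stands. A reader might infer that the sample size is wrong or that the article promises 80% power per arm. The documents support neither: 37 reproduces, and no pairwise power is claimed.

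A reader might also infer that app versus control has about 50% power and is close to uninformative. That is too strong. The 0.51 is an uncorrected interaction test. Data analysis does not fix the pairwise contrast, and Holm-adjusted app-control power runs from about 0.35 to 0.82 without baseline adjustment. The description suits therapist-app better.

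Equally, therapist-control should not be credited with 0.89 after Holm on average change. That figure ignores the gate, and no procedure gated on the interaction can exceed the omnibus power of about 0.81. The gate itself is loosely worded, since any significant overall effect opens it. If a time effect alone is enough, the ungated Holm figures apply.

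The 73% under AR(1) is what the label implies, not what was assumed. With all 50 per group, AR(1) would give 0.87 for the omnibus test, and the mixed model uses partial data. That softens the consequence but does not make the label right. At 50 per group with no dropout, change-based app-control power after Holm is still only 0.49 to about 0.73.

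**Conclusion.** The point holds as a mislabelled covariance structure and as wording that claims more than the test delivers. The 37 per group gives about 81% power for the omnibus group-by-time test with correlations near 0.40/0.32/0.25. Under the named AR(1) with 0.4 it gives about 73%. On change from baseline, app-control power is about 0.35 to 0.57 after Holm, depending on the contrast, and therapist-app power is 0.11 to 0.19. These figures rest on the article's means and SD, 37 complete patients per group and the assumed four visits. The two visit spacings tried give nearly the same results.

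**What to change.** 1. Reword the paragraph: the 80% is for the omnibus group-by-time test; name the two-parameter (linear-exponent) structure and list its correlations; note about 73% if AR(1) with 0.4 holds. This costs wording only, though the stated figures become less favourable.
2. Name the pairwise contrast and state its power with Holm and the overall-test gate included. For average change these are about 0.80 for therapist-control, 0.54 for app-control and 0.18 for therapist-app. State that non-significant pairs will be reported by their confidence interval and not as no difference. Say which overall effect opens the gate.
3. As a small analysis change, make the pairwise comparison a baseline-adjusted post-treatment contrast. At 37 per group this gives app-control about 0.90 after Holm without the interaction gate, and about 0.75 to 0.76 with it. It uses data already collected and needs no extra patients, but it changes the analysis as well as the wording, so it should be fixed before the data are analysed. It does not rescue therapist-app.

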#### Data analysis

Patients will be analyzed in the groups to which they are assigned (intention-to-treat). Descriptive statistics will be used to summarize patient characteristics per treatment group. Data will be analyzed using linear mixed-effects models with group, time and group by time interaction as fixed effects. A random intercept will be added to account for correlation between measurements coming from the same individual. When one or more overall effects are significant, post-hoc pairwise testing with Bonferroni-Holm correction for multiple testing will be performed. Missing data is assumed to be missing at random (MAR) and, thus, will be ignored in the analyses. By using mixed-effects models for the analysis, we can incorporate all information on the available time points. If more than 15% of the data is missing, a sensitivity analysis will be conducted by using multiple imputation. Results of the original analysis of the available cases will be interpreted in the context of sensitivity analysis.

Additionally, the impact of adherence, HPV status, dosimetry and mucositis on the different functional endpoints will be studied in exploratory linear mixed-effects models. Fixed main-effects and interactions with group for all these factors will be evaluated.

More details on the primary, secondary and exploratory analyses can be found in the statistical analysis plan.

A *p* value of less than 0.05 will be considered statistically significant. All analyses will be conducted using SPSS Statistics version 25 (IBM, Chicago, IL, USA) and R software (R Foundation, Auckland, New Zealand).

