### Study design

The study will be a multicenter RCT. All patients will be training five times a week during the first 4 weeks of CRT. Baseline measurements will be done before the start of CRT. Every week during the training, immediately after CRT and at 1 and 3 months following treatment, patients will be evaluated by radiation therapists and SLPs. Table 1 shows an overview of the study visits and evaluations during the study. Prophylactic swallowing exercises are the same in all groups and comprise evidence-based exercises targeting the main muscle groups involved in swallowing; namely, muscles involved in tongue strength, pharyngeal contraction and laryngeal elevation/upper esophageal sphincter opening. These strengthening exercises include tongue-strengthening exercises (TSE) and chin-tuck against resistance (CTAR) combined with an effortful swallow. First, TSE will be performed since tongue strength is the main bolus-driving force and reduced tongue strength can cause oral and pharyngeal residue and aspiration [34–36]. Second, CTAR exercises are used since they have a significant impact on the suprahyoid muscles, with a positive effect on laryngeal elevation and upper esophageal sphincter opening [37, 38]. The third exercise consists of effortful swallows in combination with the chin-tuck. Effortful swallows have been shown to improve the tongue-base posterior motion and can increase tongue-base pharyngeal-wall pressures [39]. It is hypothesized that the chin-tuck in combination with an effortful swallow stimulates the pharyngeal musculature [38].

**Table 1 Tab1:** Study visits and evaluations

			Study period				
	Enrollment	Allocation	Post allocation				
Time point	*Pre RT*	*Between enrollment and start RT*	*Weeks 1–4 of RT*	*Weeks 5–7 of RT*	*End of RT*	*1 month after RT*	*3 months after RT*
Enrollment:							
Eligibility screen	X						
Informed consent	X						
Allocation		X					
Interventions:							
*PSE – control group*			X				
*PSE – app group*			X				
*PSE – therapist group*			X				
Assessments:							
*Patient, disease and therapy characteristics*	X						
*Swallowing function*	X		X		X	X	X
*Muscle strength*	X		X		X	X	X
*Impact of mucositis*	X		X		X	X	X
*Quality of life*	X				X	X	X
*Attitudes towards exercises*			X				
*Overall fatigue*	X		X				

*RT* radiotherapy, *PSE* prophylactic swallowing exercises

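### The primary group-by-time test leaves baseline MASA-C free in each group, so it acts as an unadjusted change-score test: valid and at its stated power, but using only about half the information available on the plan's own assumptions

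*Protocol article*

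**What the plan says.** The protocol's Data analysis section gives the fixed part of the model in one sentence: "Data will be analyzed using linear mixed-effects models with group, time and group by time interaction as fixed effects". The only other component it names is a random intercept per patient. It names neither a baseline covariate nor a common baseline mean. It allows post-hoc pairwise tests with Bonferroni-Holm correction once any overall effect is significant, and refers to a statistical analysis plan (not available here) for further detail.

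The Sample size calculation section shows what the model is meant to detect, namely a "different evolution over time in the experimental groups and the control group". The type I error is 0.05 and the target power 80%. The sizing assumes a repeated-measures test of three groups by four visits with the Geisser-Greenhouse correction. It starts all groups at a MASA-C score of 195, lets them fall to 171 (control), 177 (app) and 180 (therapist), and holds them flat afterwards, with an SD of 11 throughout. On the dependence between visits, the text says that an autoregressive form "is assumed for the covariance structure between the repeated measures, with a base correlation of 0.4 and a decay rate of 0.5". The result: "A total sample size of 111 participants (37 per group), is needed".

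On timing, the Study design section says: "Baseline measurements will be done before the start of CRT". The Minimization section makes baseline dysphagia an allocation factor.

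**The concern.** If baseline is a level of the time factor and every group has its own baseline mean, a group-by-time contrast is the change from baseline in one group minus the change in another. Baseline is then subtracted in full, whatever its correlation with the later score. Adjustment would subtract only the part of baseline that predicts the later score.

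The two are close when the correlation is high. The plan assumes correlations of 0.4 or less. Below 0.5, a change score is noisier than the later score taken alone.

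Nothing in the design calls for separate baseline means. Baseline is measured before treatment in one randomized population, allocation is balanced on baseline dysphagia, and the sizing itself uses a single baseline mean. What is at stake is precision of the primary test from data the trial already collects.

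**Working it through.** **Inputs (Sample size calculation).** Means 195, then 171/177/180 at three later visits; SD 11 (variance 121); 37 per group; two-sided 0.05. The correlation statement is read as 0.4 raised to 1 + 0.5 × (d − 1)/2 for visits d steps apart, with equal spacing. This gives 0.4^1 = 0.400, 0.4^1.25 = 0.318 and 0.4^1.5 = 0.253.

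**Step 1: reproduce the plan's figure.** The noncentral F calculation for the 3 × 4 interaction with Geisser-Greenhouse correction gives power 0.82 at 37 per group (0.81 by simulation), against 0.80 stated. It reaches 80% at 36 per group, or 108 in total, against 111 stated. Other readings fit less well: plain AR(1) needs 43 per group, correlations halving at each step 41, compound symmetry 33. The interaction test in the planned random-intercept model also has power of about 0.82 at 37 per group, and about 0.93 at 50.

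**Step 2: variance at one visit.** The change score has variance 2(1 − r) × 121 and the baseline-adjusted score (1 − r²) × 121. Their ratio is 2/(1 + r).

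| r | change (× 121) | adjusted (× 121) | ratio |
|---|---|---|---|
| 0.400 | 1.20 | 0.84 | 1.43 |
| 0.318 | 1.36 | 0.90 | 1.52 |
| 0.253 | 1.49 | 0.94 | 1.60 |

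The unadjusted later score has variance 1.00 × 121, so the change score is the noisiest of the three at every visit.

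**Step 3: mean of the three post-baseline visits.**
- Unadjusted: 121 × (3 + 2 × (0.400 + 0.400 + 0.318))/9 = 70.4.
- Covariance with baseline: 121 × (0.400 + 0.318 + 0.253)/3 = 39.2.
- Change score: 70.4 + 121 − 2 × 39.2 = 113.1 (from unrounded values).
- Baseline-adjusted: 70.4 − 39.2²/121 = 57.7.

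The adjusted variance is 57.7/113.1 = 0.51 of the change-score variance.

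**Step 4: the joint test.** The post-baseline group means average 176, so the sum of squared deviations is 25 + 1 + 16 = 42, and 37 × 42 = 1,554. Dividing by the variances in step 3 gives noncentrality 1,554/113.1 = 13.7 for change and 1,554/57.7 = 26.9 adjusted. With all three visits tested jointly on 6 df, the values are 14.0 with free baseline means and 27.1 with baseline adjusted for.

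Power of the adjusted 6-df test at 37 per group is 0.98 (0.99 by simulation). Its simulated type I error with a common baseline mean is 0.047. Over all the correlation readings in step 1, power is 0.74 to 0.86 as planned and 0.98 to 0.99 adjusted.

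**Step 5: a pairwise contrast.** App versus control at 3 months (6 points), Holm over three pairs, 37 per group, by simulation:
- about 35% if the contrast is a change from baseline;
- about 54% if it compares group means at that visit;
- about 57% if adjusted for baseline.

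**The case against.** **The design meets its own target.** This stands. The interaction test matches the hypothesis that the trial was sized on and has its 80% power. A reader might infer that the trial is underpowered or its analysis biased; the documents support neither. The point is efficiency.

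**The pairwise tests need not suffer.** This also stands. A reader might infer that every pairwise contrast is much too wide and that a real 6-point app effect would probably be missed. The protocol does not say that post-hoc tests compare changes. If they compare means at a visit, step 5 shows a gap of 3 percentage points, not 22.

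**The interaction is not the only route to pairwise testing.** Correct. A significant group main effect also opens it, and that effect is not a change score; its power on the plan's inputs is about 0.92 at 37 per group. It does average in the baseline visit, where no effect can exist, and it is not the effect that was sized.

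**The statistical analysis plan may adjust for baseline.** Possibly. But the protocol is not silent: it states specific fixed effects, and its sample size follows from the unadjusted interaction. If the analysis plan adjusts, this text should be aligned with it. That baseline is a level of time is inferred from the 3 × 4 sizing layout, not stated in the Data analysis section.

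**The gain rests on planning correlations and a simplified visit schedule.** In part. At r = 0.7 the single-visit variance ratio falls to 2/1.7 = 1.18. The Outcome measures section also lists weekly MASA-C scores during the exercise weeks, which the sizing and these calculations leave out.

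**Conclusion.** The point holds for the primary group-by-time test. With baseline as one of the four sized visits and a free mean per group, the test relies on unadjusted changes and loses about half the available information on the plan's inputs (noncentrality 14.0 against 27.1; power about 0.82 against about 0.98 at 37 per group). It remains a valid test.

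This rests on the plan's SD, means and low correlations, four equally spaced visits and complete data. A higher true correlation makes the gain smaller. For pairwise tests the loss runs from slight to large according to a definition that the protocol leaves open. For muscle strength and quality of life the protocol gives no SD or correlation, so the size of the gain there is unknown, though the reasoning is the same.

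**What to change.** Change the Data analysis wording in one of two ways:
- keep baseline in the outcome vector but constrain its mean to be equal across the three groups (constrained longitudinal model); or
- take baseline out of the outcome vector and enter baseline MASA-C, and its interaction with time, as covariates.

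Name the joint test of group differences at the post-baseline visits as the primary test. Base the pairwise contrasts on the same model and say what they compare. Treat the secondary outcomes that have baseline values in the same way.

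The cost is analysis wording only: no new data and no more patients. The protocol plans no interim analysis, so the change can be made before outcomes are compared between groups.

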The different exercises described above alternate during the sessions: all subjects start their first session with TSE and perform CTAR exercises and effortful swallowing in the next session. Tongue-strengthening exercises consist of 120 tongue presses and are divided into 12 sets of 10 repetitions with a 30-s rest between sets and with the target level set at 80% of 1 repetition maximum (1RM, i.e., the maximum amount of pressure that can be generated in one repetition) [34, 40–44]. The next session CTAR exercises and effortful swallows are performed. Each CTAR session consists of 150 chin-tucks against resistance at a target level of 60–70% [45] of the 1RM (i.e., in this study, the maximum chin-tuck strength that can be generated). These chin-tucks are divided into 30 sets of five repetitions with an effortful swallow at every fifth repetition. In both tongue and chin-tuck exercises, a successful repetition was defined as reaching the target level and holding the contraction for 3 s, using the green light (TSE) as biofeedback or tactile biofeedback (CTAR). According to the principle of progressive overload, maximal tongue strength and strength of the suprahyoid muscles and correspondent levels of resistance are measured at baseline and recalculated subsequently every week [44].

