All subjects will be randomly assigned into the previously defined groups: control group, app group and therapist group. The groups differ in degree and kind of adherence-improving measures. All groups have some of these measures in common. Restricting the duration to the first 4 weeks of CRT is a first method to increase compliance since the literature shows that in the last 2–3 weeks of therapy the feasibility of completing exercises decreases [20, 33]. Receiving visual and tactile feedback on their performance via the therapeutic devices is a second method. The differences in adherence-improving measures between the groups are illustrated in Table 2. The first group (control group) will perform the exercises at home, without supervision of a SLP but with a counseling session of 10 min every week. Group 2 (app group) practices at home but receives continuous counseling and gets instructions by videos via an application on a tablet, developed in collaboration with Cyborn, Antwerp, Belgium (www.cyborn.be). Generally, mobile health applications are considered to be possible tools to improve traditional health care [46]. By means of gamification, the app helps, supports and motivates the patients to practice. The app registers when the patients practice, how many repetitions they do and when they succeed in doing the exercises. Group 3 (therapist group) is given face-to-face therapy and will be counseled by a SLP five times per week. All patients will complete the first session with supervision of the SLP, irrespective of their group. The intervention will be discontinued on participant request or in case of worsening disease, requiring major changes in treatment. Reasons for discontinuing will be stored in a database.

**Table 2 Tab2:** Study design

Inclusion	*n* = 150		
Stratified randomization	*n* = 50 Control group	*n* = 50 App group	*n* = 50 Therapist group
Therapy schedule	• 5x/week (30–40 min)	• 5x/week (30–40 min)	• 5x/week (30–40 min)
	• 4 weeks	• 4 weeks	• 4 weeks
	• Home practice	• Home practice but app-supported	• Therapist supervised
Exercises	• TSE	• TSE	• TSE
	• CTAR	• CTAR	• CTAR
	• Effortful swallow	• Effortful swallow	• Effortful swallow
Adherence measurements			
• Supervision	No (home practice)	No (home practice – app)	Yes (face-to-face therapy)
• Counseling	Counseling 1x/week by SLP (10′)	Counseling 1x/week by SLP (10′) & continuous counseling via app	Counseling by SLP 5x/week

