### Outcome measures

The primary outcome measure of this study is the swallowing function, based on scores of the Mann Assessment of Swallowing Ability-Cancer (MASA-C) [49]. Next to this measurement, patients are asked to fill out the Eating Assessment Tool-10 [50] and a Visual Analog Scale. The Functional Oral Intake Scale [51] is filled in by a SLP. The swallowing function is assessed at baseline, weekly during the weeks of exercise, immediately after CRT and 1 and 3 months after CRT (Table 1).

There are three secondary outcome measures: (1) degree of compliance, (2) muscle strength and (3) QOL.

The degree of compliance is expressed as the total number of exercises performed per week, based on daily patient (group 1 and 2) and therapist (group 3) registration. The number of performed tongue-strengthening exercises is recorded automatically by means of the IOPI. In group 2, the degree of compliance is also expressed by the time spent on the app, which is registered automatically. The compliance is assessed during the first 4 weeks of CRT. MIP_a_, MIP_p_ and strength of the suprahyoid muscles are examined at the same time as the swallowing function (Table 1) and are measured using the IOPI and a dynamometer. The Swallowing Quality-of-Life Questionnaire [52] and the Dysphagia Handicap Index [53] examine the swallowing-related QOL and are assessed at baseline, at the end of CRT and 1 and 3 months after CRT (Table 1).

All these evaluations are performed by a SLP.

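### One mixed model with a random intercept and no arm-specific variance is stated for all outcomes; for weekly compliance, the app-versus-control error rate would then depend on the spread in the therapist arm

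*Protocol article*

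**What the plan says.** The Data analysis section sets one approach without separating outcomes: "Data will be analyzed using linear mixed-effects models with group, time and group by time interaction as fixed effects". It continues: "A random intercept will be added to account for correlation between measurements coming from the same individual". A significant overall effect opens pairwise tests with Bonferroni-Holm correction, at a 0.05 level. The section names no other model for any outcome and no variance that differs by arm. It refers to the SAP for further detail.

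The Outcome measures section makes compliance secondary: "There are three secondary outcome measures: (1) degree of compliance, (2) muscle strength and (3) QOL". It defines the measure: "The degree of compliance is expressed as the total number of exercises performed per week". Compliance is recorded over the first four weeks of treatment.

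The Study design section sets the schedule: "All patients will be training five times a week during the first 4 weeks of CRT". It alternates two session types: "Tongue-strengthening exercises consist of 120 tongue presses" and "Each CTAR session consists of 150 chin-tucks against resistance". The same section separates the arms by supervision. The therapist arm "is given face-to-face therapy and will be counseled by a SLP five times per week", while Table 2 lists both other arms as unsupervised home practice.

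**The concern.** A linear mixed model with a plain random intercept is normally fitted with one between-patient and one residual variance for all arms. Every pairwise contrast then draws its standard error from all three arms, including the arm that is not being compared.

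For a count with a practical upper limit, arms with different means tend to have different variances. Here the arms differ by design in something the Background section itself names as a cause of non-adherence, the absence of supervision. If the therapist arm has the smallest spread, the pooled variance is too small for app versus control and too large for contrasts with the therapist arm. If it has the largest spread, the reverse holds. Equal arm sizes do not remove the problem.

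App versus control on compliance is the most direct evidence on whether the app improves adherence. A wrong standard error could create an app effect or hide one.

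**Working it through.** **The plan's own figure.** The article gives no mean, SD or error rate for compliance. Its only calculation is for MASA-C: 37 per group for 80% power. With means of 195 at baseline then 171/177/180, SD 11, base correlation 0.4 and decay rate 0.5 (correlations 0.40, 0.32, 0.25 at lags 1 to 3), simulated power of the Geisser-Greenhouse-corrected group-by-time test at 37 per group is 0.806. The figure reproduces. The target of 150 leaves room for 1 − 111/150 = 26% dropout, consistent with the stated allowance. None of this depends on compliance.

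**Step 1: the limit on the count.** Counting repetitions, with alternating sessions, tongue exercises first and five sessions a week:
- week with three tongue sessions: 3 × 120 + 2 × 150 = 660
- week with two tongue sessions: 2 × 120 + 3 × 150 = 690

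**Step 2: size of the test under a pooled variance.** Let the control and app arms share SD s, let the therapist arm have SD r·s, and let each arm have n patients. In the balanced random-intercept model the group contrast is a contrast of patient means.
- Pooled variance: (s² + s² + r²s²)/3 = s²(2 + r²)/3
- True variance of app minus control: 2s²/n
- Variance the model uses: (2s²/n) × (2 + r²)/3
- True size of a nominal 5% test (large n): 2 × [1 − Φ(1.96 × √((2 + r²)/3))]

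Example, r = 0.5: (2 + 0.25)/3 = 0.75; √0.75 = 0.866; 1.96 × 0.866 = 1.697; size 9.0%.

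| r (therapist SD / home SD) | true size |
|---|---|
| 0 (limit) | 11.0% |
| 0.25 | 10.4% |
| 0.5 | 9.0% |
| 0.75 | 7.0% |
| 1 | 5.0% |
| 1.25 | 3.3% |
| 2 | 0.6% |

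**Step 3: contrasts with the therapist arm.** The true variance is s²(1 + r²)/n. At r = 0.5 the model uses 2 × 0.75 = 1.50 in units of s²/n where 1.25 is correct, so the standard error is too large by √(1.50/1.25) = 1.095, about 10%.

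**Step 4: simulated bounded counts, with the overall test and Holm over three group contrasts.** App and control are identical, with 50 per arm. Means and SDs are percentages of the schedule, and all are assumptions.

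| control and app: mean (SD) | therapist: mean (SD) | app-vs-control error |
|---|---|---|
| 50 (30) | 95 (5) | 10.8% |
| 50 (30) | 90 (10) | 10.1% |
| 50 (30) | 85 (15) | 8.9% |
| 64 (30) | 85 (20) | 7.1% |
| 64 (30) | 75 (25) | 3.3% |
| 90 (10) | 95 (5) | 5.3% |
| 50 (30), 20% of each arm stop early | 95 (5) before stopping | 5.8% |
| 64 (25), 20% of each arm stop early | 95 (5) before stopping | 5.5% |
| 13 (15) | 64 (30) | 0.6% |

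In the stopping rows, patients who stop are scored zero afterwards. This raises the SD ratio to about 0.87 to 0.91. Another set of simulated trials gave 6 to 7% for 20% early stopping, and 10.7%, 8.8% and 7.7% for therapist SDs of 8, 15 and 20 against 30 at home.

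The 3.3% and 5.3% rows fall below their unadjusted sizes (6.5% and 8.6%) because the therapist contrasts are not always both rejected, so Holm keeps a stricter threshold. Once both are rejected, app versus control is tested at the full 0.05 and Holm gives no protection.

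**Step 5: the remedy.** With the variance taken from the two compared arms only, the error was 4.7% to 5.3% in every scenario.

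**The case against.** The strongest reply has four parts.

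*The article never says that one variance is pooled, and it defers detail on secondary outcomes to a SAP that is not shown.* This stands in part. Pooling is the ordinary reading of the stated model, not its wording. But the article does state a model family and a random structure for all data, so the point concerns a stated method and not a missing detail. If the SAP treats compliance differently, the point is closed.

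*Nothing in the article supports a particular SD ratio.* This stands. A reader might infer that the supervised arm will sit near its ceiling and that the false-positive rate therefore doubles. The article does not support that. It reports only that an earlier three-arm trial found significantly better adherence with face-to-face therapy, with no rate or SD, and it allows discontinuation in every arm. The 13 to 64% in the Background section is a range of rates across studies. It is not the spread between patients in a home arm.

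*The cap is not part of the definition.* Also fair: compliance is the number of exercises performed, and the text does not cut it off at the prescription. The schedule is a practical limit. The formula in Step 2 needs only unequal variances, not a hard cap.

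*The Holm argument assumes a family of three group contrasts.* The article does not define the family. With week-by-week contrasts, app versus control would not be released at 0.05 after only two rejections. The distortion remains at a stricter threshold, however: at 0.05/3 (1.7%) the same formula gives 3.8% for r = 0.5 and 5.1% for r = 0.

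**Conclusion.** The concern holds in conditional form. If the stated model is fitted to compliance with one variance across arms, the app-versus-control error rate is governed partly by an arm outside the comparison. The possible range is wide: at most about 11% when the therapist arm has almost no spread, about 8 to 9% at half the home-arm SD, roughly 5 to 7% when some patients in every arm stop early, and below 1% when the home arms are near the floor. A doubled error rate is the upper end of that range and should not be read as the expected result.

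The conclusion rests on assumed means and SDs, on near-equal arm sizes (the plan allocates 1:1:1), on pooling as the usual reading of the text, and, for the simulated figures, on a family of three group contrasts. It concerns one secondary outcome. The primary MASA-C analysis and the sample size are untouched, and nothing computed here bears on the other scales. Because unequal variances are foreseeable from the design and the error can go either way, the method is worth correcting before the data are analysed.

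**What to change.** For the compliance outcome only, add a sentence to the SAP, unless it already says this: the linear mixed model will allow between-patient and within-patient variances to differ by arm, or all pairwise contrasts will use small-sample cluster-robust (CR2) standard errors. Either choice makes each contrast reflect the spread of the arms being compared, whichever direction the imbalance takes.

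The cost is a few lines of R, which the article already lists as planned software, and slightly fewer degrees of freedom per contrast. Sample size, visits and data collection do not change.
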